## Abstract

**Background:**

Type 2 diabetes (T2D) is increasing as the population ages. The development of new medical treatments is promising and important, but the basic treatment remains self-management, even if adherence to lifestyle advice is low. Electronic health (eHealth) or mHealth interventions can increase empowerment among people living with T2D and may compensate for the lack of professional resources and geographical distances. The interactive self-management support (iSMS) project aims at including digital tools to support people living with T2D in their self-management and facilitating their interaction with diabetes specialist nurses (DSNs). This protocol outlines a study with the purpose of developing and evaluating an intervention where people living with T2D can increase self-efficacy and empowerment through digital self-monitoring and interaction with DSNs.

**Objective:**

To develop and evaluate a person-centered iSMS intervention in primary health care for people with T2D in addition to their usual diabetes care.

**Methods:**

This study is a 12-month, 3-armed, nonblinded randomized controlled trial (RCT), which will be conducted in 6 primary health care centers (HCCs) in northern Sweden. Eligible participants will be randomized to either an intervention group (n=46), a control group (n=46), or an external group (n=46) for comparison. The intervention group will receive the mobile app, and the control group will receive a minimal intervention (diabetes brochure) and the usual standard of care. Changes in glycated hemoglobin (HbA_1c_) will be the primary outcome measure.

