The purpose of the interactive self-management support (iSMS) project is to include digital tools by offering the use of a smartphone or tablet app to support people living with T2D in self-management and to facilitate interaction with DSNs. This study protocol outlines a randomized controlled trial (RCT) to evaluate the effectiveness of person-centered iSMS in primary health care. This study puts a particular focus on how digital technology is used as a tool for self-management in daily life, wherein patients with T2D manage their illness in closer collaboration with DSNs through self-monitoring and self-care activities. The objectives of this project are to develop and evaluate a person-centered iSMS intervention in primary health care for people with T2D in addition to their usual diabetes care. The hypotheses are that an iSMS program will decrease glycated hemoglobin (HbA_1c_) and improve metabolic measurements, such as BP (mm HG), body mass index, waist circumference (cm), and total and high-density lipoprotein cholesterol (mmol/L). Furthermore, we hypothesize that an iSMS program will improve lifestyle habits such as physical activity, diet, and smoking; decrease the need for SMS and changes in medical treatment; increase diabetes empowerment; increase diabetes-dependent quality of life (QoL); improve illness perception; and improve eHealth literacy in the intervention group compared with an internal (intervention and control) and external control group at 4 and 12 months’ follow-up.

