## Methods

### Trial Design

This protocol describes a 3-armed, nonblinded RCT to evaluate the effectiveness of person-centered iSMS in primary health care on metabolic balance, as measured by HbA_1c_. Within this project, interactive SMS (iSMS) is defined as person-centered and interactive self-management support. The person-centered part lies in an assessment of individual needs for SMS through a quantitative measurement and by listening to patients’ stories. The interactive part lies in the patients’ use of a smartphone or tablet app for self-monitoring and also interaction with the nurse and other participants through a patient forum when needed. Furthermore, other digital sources, such as a website with information about T2D, self-care, and so forth, will be included in the intervention. This protocol was prepared according to the Consolidated Standards of Reporting Trials [27], the Consolidated Standards of Reporting Trials extension for Electronic and mobile Health Applications and onLine TeleHealth interventions [28], and the Standard Protocol Items: Recommendations for Intervention Trials guidelines [29,30].

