### Randomization and Blinding

Eligible participants will be randomized to either the intervention or the control groups in a 1:1 ratio. Owing to the nature of the intervention, participants will be aware of their treatment allocation. Therefore, the blinding of participants will not be possible. However, DSNs in charge at HCCs will not be involved in the randomization, preparation of the envelopes with study information, or statistical analyses.

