#### Inclusion Criteria

Eligible participants are adult, aged ≥18 years, patients with T2D diagnosed within the last 5 years, Swedish-speaking, noninsulin-treated at inclusion, and own a smartphone. They will be randomized to either an intervention group (n=46) or a control group (n=46). An external comparison group (n=46) will be recruited from 2 different HCCs to analyze for a possible Hawthorne effect. The recruitment process will start in September 2018. The study flow chart is presented in Figure 1.

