### Data Analyses

All analyses to evaluate change over time with regard to intervention outcomes will be made with the intention-to-treat principle, which means that all participants are analyzed according to the group they were randomized into [50]. Appropriate imputation methods will be applied to the missing data.

Baseline and sociodemographic characteristics will be summarized using descriptive statistics. Continuous variables will be summarized as numbers of observed values and mean (SD) or median and quartiles when appropriate. Categorical variables will be described using central tendencies and variability. Differences between groups will be analyzed using inferential statistics.

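### The external group is presented as a third randomised arm, but the Methods recruit it from two different health centres, so contrasts with it are non-randomised and confounded with centre

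*Protocol article*

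**What the plan says.** The protocol article gives two accounts of how the external group is formed.

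**Randomised third arm.** The abstract (Methods) describes a "3-armed, nonblinded randomized controlled trial (RCT), which will be conducted in 6 primary health care centers (HCCs) in northern Sweden" and continues: "Eligible participants will be randomized to either an intervention group (n=46), a control group (n=46), or an external group (n=46) for comparison". Trial Design repeats the label: "This protocol describes a 3-armed, nonblinded RCT to evaluate the effectiveness of person-centered iSMS in primary health care on metabolic balance".

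**Separately recruited cohort.** Randomization and Blinding says: "Eligible participants will be randomized to either the intervention or the control groups in a 1:1 ratio". Inclusion Criteria names the same two randomised groups, 46 each, and then adds: "An external comparison group (n=46) will be recruited from 2 different HCCs to analyze for a possible Hawthorne effect".

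Two further places depend on which account is true. The hypotheses at the end of Background have the intervention group "compared with an internal (intervention and control) and external control group at 4 and 12 months’ follow-up". Data Analyses applies intention-to-treat to all analyses of change over time, explained as meaning that "all participants are analyzed according to the group they were randomized into".

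Study Population and Sampling also says that patient recruitment uses a clustered RCT design, which does not fit 1:1 randomisation of participants.

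**The concern.** Whether a comparison is randomised decides whether a difference can be attributed to the intervention without further assumptions. If the operative Methods sections are right, no chance mechanism places anyone in the external group. Membership follows from the centre where a patient is treated. Differences in case mix, prescribing or staff between centres then cannot be told apart from an effect of the programme.

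The hypotheses name the internal and external comparators together and give the external one no lesser status. The intention-to-treat rule has no meaning for participants who were never randomised. A reader of the abstract would credit the contrast between intervention and external group with a protection that it does not have.

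**Working it through.** **1. The plan's own figure.** Power Calculation and Sample Size gives 46 per group, a difference of 6 mmol/mol, SD 9, 80% power and alpha 0.05 (two-sided assumed).
- n per group = 2 × (1.96 + 0.842)² × (9/6)² = 35.3, so 36.
- With 46 per group, SE = 9 × √(2/46) = 1.88, and power = Φ(6/1.88 − 1.96) = 0.89.

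So 46 does not reproduce as the number needed for 80% power. That is a separate matter. What counts here is that the section interprets its power for intervention against control only.

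**2. The passages side by side.**

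| Section | External group |
|---|---|
| Abstract, Methods | Randomised, one of three |
| Trial Design | One arm of a three-armed RCT |
| Randomization and Blinding | Not among the groups randomised |
| Inclusion Criteria | Recruited from two different centres, for a Hawthorne check |
| Background, hypotheses | Comparator for effectiveness |
| Data Analyses | Under intention-to-treat by randomised group |

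The first two rows cannot both stand with the next two. The sections that describe the procedure agree with each other, so the external group is not randomised.

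**3. Confounding with centre.** On the plain reading, the two external centres supply no randomised participants. The indicator for external group is then the sum of the indicators for those two centres, so no model with fixed centre effects can separate group from centre. The article does not say whether the two centres are among the six or additional. Either way the group is defined by centre.

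The same holds for the Hawthorne contrast. Control Groups (plural) appears to give both control groups the same brochure, usual care and data collection. A difference between them could reflect study conditions at the randomising centres or simply the centres themselves.

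**4. Illustration of size.** Only SD 9 and 46 per group come from the document. Assumed: intraclass correlation (ICC) of 0.02 to 0.05; two external centres with equal numbers; k = 4 or 6 centres supplying the intervention arm (six less the two external ones, or all six).
- Between-centre variance = ICC × 81; within-centre variance = (1 − ICC) × 81.
- SE = √[between × (1/2 + 1/k) + within × 2/46].
- Actual error of a nominal 5% patient-level test = 2 × [1 − Φ(1.96 × 1.88/SE)].

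| ICC | Centre SD | k | 95% shift from centre alone | SE | Type I error |
|---|---|---|---|---|---|
| 0.02 | 1.27 | 6 | ±1.96 × 1.04 = ±2.0 | 2.13 | 8.4% |
| 0.02 | 1.27 | 4 | ±1.96 × 1.10 = ±2.2 | 2.16 | 8.9% |
| 0.05 | 2.01 | 6 | ±1.96 × 1.64 = ±3.2 | 2.46 | 13.5% |
| 0.05 | 2.01 | 4 | ±1.96 × 1.74 = ±3.4 | 2.53 | 14.5% |

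Shifts and SEs are in mmol/mol. At ICC 0.01 the error is 6.7% to 6.9%, and at 0.10 it is 20.9% to 22.6%. These figures cover random centre variation only. Systematic differences from non-random selection would come on top and cannot be computed from the document.

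**The case against.** The strongest reply is that the Methods already hold the correct design. They randomise two groups, recruit the third separately and say why. Separate centres are a legitimate choice for a Hawthorne check. On this view the fault is a loose abstract sentence and a loose label, and the comparison that was powered is untouched. All of that stands, and it limits the point. It does not remove it, because the hypotheses take the external group beyond the Hawthorne purpose and use it to judge effectiveness.

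Second, the intention-to-treat clause may be only a textbook gloss, naturally read as covering those who were randomised. That is fair. It adds little harm of its own, but it should be worded to fit the design.

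Third, the error rates rest on assumptions. The primary outcome is change in HbA1c, and stable differences between centres cancel at least in part in a change score. The article does not say whether SD 9 refers to level or to change. No test that ignores centre is specified. This also stands: the figures are illustrative, and the point does not depend on them.

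Fourth, a reader might infer that a significant difference from the external group would be reported as a randomised result. The article does not say so. Data Analyses names no test and no ranking of contrasts, and an analysis plan that is not shown may deal with it.

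Finally, the clustered design wording might suggest that centres were allocated at random. The article does not say that any centre was randomised to the external group. Even if it were so, two external centres would be too few to separate group from centre.

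**Conclusion.** The point holds as an error in how the design is stated. The abstract and Trial Design give the external group a randomised status that Randomization and Blinding and Inclusion Criteria contradict. It is a concurrent, non-randomised cohort of 46, and on the plain reading of its recruitment every contrast with it is confounded with centre. This changes what the trial can conclude from that contrast, because the effectiveness hypotheses use it.

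The documents do not support the wider reading that the trial's main result is compromised. The powered comparison of intervention with internal control is untouched by this point. Nor is a type I error of 8% to 15% a property of the plan. It follows only from an assumed ICC of 0.02 to 0.05, SD 9, two external and four to six intervention centres, and a test that ignores centre. It may be lower if centres vary less in HbA1c change than in level.

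**What to change.** - Describe the study throughout as a two-arm randomised comparison (46 against 46) with a non-randomised external comparison group (n=46). Bring the abstract, the Background hypotheses, Trial Design and Data Analyses into line with Randomization and Blinding and Inclusion Criteria.
- Reconcile the clustered design wording in Study Population and Sampling with the 1:1 randomisation of participants, so that the unit of randomisation is stated once. State whether the two external centres are among the six or additional.
- Limit the confirmatory hypothesis and intention-to-treat to intervention against internal control.
- Report contrasts with the external group, including the Hawthorne comparison, as secondary and observational, adjusted for baseline, with the confounding by centre stated.
- Clarify in Background what the internal comparator is. The present phrase puts the intervention group inside its own comparator.

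The cost is wording and a weaker claim against the external group. No participants, visits or measurements change.

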**Results:**

This trial is currently open for recruitment. The first results are expected to be submitted for publication in Autumn 2019.

**Conclusions:**

This study, with its focus on iSMS, will provide insights regarding suitable ways to promote and develop a person-centered intervention. If successful, the intervention has the potential to become a model for the provision of self-management support to people with T2D.

**International Registered Report Identifier (IRRID):**

DERR1-10.2196/10250

## Introduction

### Background

Type 2 diabetes (T2D) occurs in up to 20% of people aged ≥70 years. T2D is a progressive disease with an increased risk of cardiovascular disease, cancer, and dementia. Physical inactivity and being overweight owing to an unhealthy lifestyle, such as that involving the use of tobacco and alcohol consumption, are key factors in the progression of T2D [1,2]. T2D requires both active self-management of people living with the disease and advanced medical treatment over time [1,2,3]. About 350,000 people living in Sweden are diagnosed with T2D [3], and the risk increases with age, regardless of gender [2,3]. Education levels relate to diabetes development, the higher the education, the lower the incidence. The incidence also varies by country (of birth) with higher prevalence among people born in the Nordic countries than in Europe outside Scandinavia [3].

Caring for people with T2D is a challenge for society, especially in rural areas that suffer from a shortage of general practitioners in primary health care [4]. In Sweden, primary health care nurses with responsibility for diabetes clinics (diabetes specialist nurses, DSNs) have a heavy workload and are often responsible for a large number of T2D patients regarding self-management support (SMS) and follow-ups. SMS includes motivating T2D patients to quit smoking, increase physical activity, change diet, initiate weight loss, and adhere to medication and blood sugar testing [5], all examples of frequent work tasks that fall on DSNs. The medical treatment is multifactorial and includes monitoring of blood sugar targets, blood pressure (BP), blood lipids, and other medical measures [6]. Furthermore, preventive measures such as retinal scans [7] and annual foot examinations are of great importance for delaying complications [8].

T2D is a complex disease with complex treatment, in which self-management is the basic treatment [9-11]. In recent years, SMS in groups and culturally appropriate education have been recommended, led by staff with both subject expertise and pedagogical training [3]. Findings in studies [10,12] show that SMS or patient education in groups and directed to individuals are equally effective among people with T2D and result in similar improvements in learning, behavioral, and clinical outcomes. In diabetes care, there have to be various individual options and scope for those who do not want to participate in or fit into groups. Additionally, person-centered care (PCC) that enables custom solutions and person-centered approaches that strengthen self-efficacy and patient empowerment are beneficial [10,13-14]. Electronic health (eHealth) interventions for chronically ill patients, instead of or in addition to usual care, can lead to positive effects on primary health outcomes [15]. eHealth interventions are also requested today and are motivated not only by the problems of geographical distance [16] and lack of health care staff [17] but also by the opportunities offered by the approach, namely, strengthened power and ownership as well as increased person-centeredness. Therefore, we believe that it is important to develop SMS using an eHealth intervention.

Recent research suggests that patients view the use of smartphone apps for self-monitoring and channels aimed at social support and interaction with the caregiver via computers and smartphones [18] as a good and important complement to traditional care. Some patients, however, express doubt about the technological issues that may arise [19]. A challenge may also be health care staff’s hesitation to use eHealth and mobile health in patient care. A recent interview study [20] among nurses in primary health care indicates that they viewed the trend toward eHealth approaches in patient care as unavoidable. However, the transition from traditional face-to-face visits to eHealth support could lead to a lack of control in their daily work, and they expressed a need to protect both themselves and the patients in the digital chaos created [20,21]. They preferred to meet patients face-to-face and saw a risk in the ongoing role change that may lead to losing their expert role in providing practical advice to patients. The solution could be to involve patients with T2D and DSNs in working together to develop an intervention with both obstacles and opportunities within their respective perspectives in mind. Several researchers recommend this kind of co-design and participatory design [22-24] since the implementation of new ideas is facilitated; these become accepted by users and are thereby longer-term solutions.

The purpose of the interactive self-management support (iSMS) project is to include digital tools by offering the use of a smartphone or tablet app to support people living with T2D in self-management and to facilitate interaction with DSNs. This study protocol outlines a randomized controlled trial (RCT) to evaluate the effectiveness of person-centered iSMS in primary health care. This study puts a particular focus on how digital technology is used as a tool for self-management in daily life, wherein patients with T2D manage their illness in closer collaboration with DSNs through self-monitoring and self-care activities. The objectives of this project are to develop and evaluate a person-centered iSMS intervention in primary health care for people with T2D in addition to their usual diabetes care. The hypotheses are that an iSMS program will decrease glycated hemoglobin (HbA_1c_) and improve metabolic measurements, such as BP (mm HG), body mass index, waist circumference (cm), and total and high-density lipoprotein cholesterol (mmol/L). Furthermore, we hypothesize that an iSMS program will improve lifestyle habits such as physical activity, diet, and smoking; decrease the need for SMS and changes in medical treatment; increase diabetes empowerment; increase diabetes-dependent quality of life (QoL); improve illness perception; and improve eHealth literacy in the intervention group compared with an internal (intervention and control) and external control group at 4 and 12 months’ follow-up.

### Theoretical Framework

This randomized intervention study is grounded on the theoretical perspectives of PCC, which is a care model that supports the person’s views about their life situation and condition as being indisputable and is always at the center of care. According to PCC, patients are persons who are more than their illness. PCC is based on the patient’s experience of the situation and the individual’s circumstances, resources, and obstacles. PCC has been described as the gold standard of care that will help individuals to develop the knowledge, skills, and confidence they need to more effectively manage and make informed decisions about their health or illness and health care and thus become partners in care. It also means that the patient should always be treated with respect. PCC is a partnership between patients or relatives and professional caregivers. It requires that health care professionals and patients together lay the ground for a relationship or partnership. The starting point for PCC is the patient’s story, which should be written in a structured way into a health plan that includes the goals and strategies for implementation and short- and long-term follow-up [25,26]. By shifting from an illness focus to a strengths-based, person-centered one, this intervention may change the usual care for people with T2D in primary health care. The process is intended to develop and implement an actionable plan to assist people with T2D in achieving their personal goals in the “illness process”. This RCT is intended to address the specific barriers that interfere with the person’s personal goal achievement; the aims are to transform and offer the participants a process for sustainable behavior change to fulfill their personal goals.

## Methods

### Trial Design

This protocol describes a 3-armed, nonblinded RCT to evaluate the effectiveness of person-centered iSMS in primary health care on metabolic balance, as measured by HbA_1c_. Within this project, interactive SMS (iSMS) is defined as person-centered and interactive self-management support. The person-centered part lies in an assessment of individual needs for SMS through a quantitative measurement and by listening to patients’ stories. The interactive part lies in the patients’ use of a smartphone or tablet app for self-monitoring and also interaction with the nurse and other participants through a patient forum when needed. Furthermore, other digital sources, such as a website with information about T2D, self-care, and so forth, will be included in the intervention. This protocol was prepared according to the Consolidated Standards of Reporting Trials [27], the Consolidated Standards of Reporting Trials extension for Electronic and mobile Health Applications and onLine TeleHealth interventions [28], and the Standard Protocol Items: Recommendations for Intervention Trials guidelines [29,30].

